### Trial Site and Sample Size Calculation

The trial will be conducted at the Department of General, Visceral and Transplantation Surgery at the University Hospital of Heidelberg. Prevalence of malnutrition in pancreatic cancer is known to be 88% [30]. We calculated sample size with a lower prevalence of 70% for all pancreatic diseases. With a specificity and sensitivity of 95% and a confidence interval of 0.05, a total of 260 patients will be needed [31]. Patients will be consecutively recruited until the study population will consist of 260 patients with major pancreatic resections (pancreaticoduodenectomy, distal pancreatic resection, or total pancreatectomy). Based on the department’s data (about 500 eligible pancreatic resections), recruitment will be completed within 12 months after inclusion of the first patient.

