### Diagnostic Intervention (Nutritional Assessment Scores)

Based on the most recent systematic review about existing nutritional assessment scores by Van Bokhorst-de van der Schueren [12], 11 scores have been selected that are in use in surgical patient populations [18-27]. Recently, the European Society of Clinical Nutrition and Metabolism (ESPEN) published a new consensus definition of malnutrition, the ESPEN malnutrition criteria [28]. Table 1 presents a summary of the 12 nutritional assessment scores that will be evaluated.

**Table 1 table1:** Nutritional assessment scores.

Name	Classification for nutritional risk^a^
Nutritional Risk Index [18]	Normal/mild/moderate/severe
Nutritional Risk Screening Score and Revised Version [19,26]	Low/ moderate/high
Subjective Global Assessment [20]	No/ moderate/severe
Malnutrition Universal Screening Tool [21]	Low/ medium/high
Mini-Nutritional Assessment and Revised Version [22,27]	Normal/ at risk/malnourished
Short Nutritional Assessment Questionnaire [23]	Low/ moderate/severe
Imperial Nutritional Screening System I [24]	Not at risk/at risk
Imperial Nutritional Screening System II [24]	Green/amber/red
Nutritional Risk Classification [25]	Low/at risk
ESPEN Malnutrition Criteria [28]	Normal/malnourished

^a^The highest class for nutritional risk determined by the scores will be used as the study end point “at risk for malnutrition” for statistical evaluation.

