### Outcome Measures

The primary end point is postoperative morbidity and mortality. The most suitable score is defined as the score with the highest association of malnutrition and postoperative complication expressed as the highest lower bound of the 95% confidence interval of odds ratio.

Secondary end points are length of hospital stay, length of stay in intensive care unit, comprehensive complication index [29], place of discharge (discharge to home or discharge to rehabilitation or care facility), necessity of postoperative parenteral or enteral nutrition, and impact of malnutrition as diagnosis on hospital costs and Diagnosis Related Group (DRG) case cost.

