### Statistical Analysis

The included scores use different numbers of nutritional risk classes. To compare the scores, evaluation of the primary end point patients will be dichotomized by each nutritional assessment score as “at risk” or “not at risk” using the respective highest nutritional risk determined by each score (Table 1). Further, patients will be dichotomized whether they had at least one major complication (Clavien-Dindo III-V) or not. Hence, for every nutritional assessment score, a contingency table will be created (Figure 1). Positive predictive value, specificity, sensitivity, and c-index will be calculated. Association between every nutritional assessment score and major complication will be expressed as odds ratio with 95% confidence interval. Univariable significance of association will be tested with a chi-square test without Yate’s correction at a level of significance of 5%. A multivariable logistic regression model will be used for evaluation of primary end point at a level of significance of 5%. Covariates will be age (years) and operation time (minutes). Factors will be malignancy; gender; laparoscopy; intraoperative radiotherapy; resection of vessels (portal vein, superior mesenteric artery, or vein); inclusion in an interventional trial; American Society of Anaesthesiologists (ASA) physical status classification system; prior upper gastrointestinal surgery; pancreatic surgery associated risks (amylase in drainage >5000 IE/U on POD 1, biliary stent); and preoperative serum albumin level less than 35 g/L. Subgroup analysis will be performed separately for different types of pancreatic resections and different nutritional risk classes will be determined by each score (Table 1).

Secondary end points will be analyzed descriptively by tabulation of the measures of the empirical distributions. According to the level of the variables, means, SDs, medians, 1st and 3rd quartiles, minimum and maximum, or absolute and relative frequencies will be reported, respectively. Descriptive *P* values of the corresponding statistical tests and associated 95% confidence intervals will be given. Statistical analysis will be performed with program R [43].

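### The 260 patients are justified by malnutrition prevalence, but the analysis shown measures accuracy against major complications and picks the score by an odds ratio bound, so the stated precision is not assured

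*Protocol article*

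**What the plan says.** Under Trial Site and Sample Size Calculation, the protocol article starts from an 88% prevalence of malnutrition in pancreatic cancer and lowers it: "We calculated sample size with a lower prevalence of 70% for all pancreatic diseases". It then concludes: "With a specificity and sensitivity of 95% and a confidence interval of 0.05, a total of 260 patients will be needed".

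The footnote to Table 1 defines how each score is used: "The highest class for nutritional risk determined by the scores will be used as the study end point", meaning being at risk for malnutrition. Under Statistical Analysis the other margin of the contingency table is the complication outcome: "Further, patients will be dichotomized whether they had at least one major complication (Clavien-Dindo III-V) or not". From that table, "Positive predictive value, specificity, sensitivity, and c-index will be calculated".

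Under Outcome Measures the most suitable score is the one with the strongest association between malnutrition and complications, "expressed as the highest lower bound of the 95% confidence interval of odds ratio".

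**The concern.** A precision calculation for sensitivity and specificity divides the patients into those with and those without the condition to be detected. The prevalence it uses must therefore be that of the condition. The sample size paragraph uses malnutrition as the condition. The analysis uses malnutrition as the test result and a major complication as the condition. The two calculations concern different tables.

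The selection rule adds a second gap. The score is chosen by a bound on an odds ratio, yet no complication rate, odds ratio or interval width for an odds ratio enters the calculation.

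The aim is to choose one of 12 scores, and the Discussion expects later intervention trials to build on that choice. A reader who takes the sample size paragraph at face value will expect accuracy estimates good to 5 points, and cannot tell what strength of association 260 patients can show.

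**Working it through.** **Inputs from the protocol article.** Prevalence 0.70 (malnutrition); sensitivity = specificity = 0.95; interval 0.05, read as a half-width d; N = 260. Taking z = 1.96 is an assumption for the sample size paragraph; the 95% level is stated for the analysis.

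**1. The plan's own figure.** Patients needed in each condition group: z²·p(1−p)/d² = 1.96² × 0.95 × 0.05 / 0.05² = 72.99.
- Sensitivity: 72.99 / 0.70 = 104.3, so 105.
- Specificity: 72.99 / 0.30 = 243.3, so 244, which governs.

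The stated 260 is slightly larger. Rounding z to 2 gives 254. With 260 patients, 182 malnourished and 78 not, the half-widths for detecting *malnutrition* would be 3.2 points (sensitivity) and 4.8 points (specificity). The calculation is coherent for that target.

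**2. The same formula with the condition used in the analysis.** The article gives no major complication rate π. I assume 20-35%, that is 260 × 0.20 = 52 to 260 × 0.35 = 91 events, and 208 to 169 patients without an event. Half-width for sensitivity: 1.96·√(s(1−s)/(260π)). For specificity, 260(1−π) replaces 260π.

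| True value | Sensitivity, π = 20% | Sensitivity, π = 35% | Specificity, π = 20% | Specificity, π = 35% |
|---|---|---|---|---|
| 95% | 5.9 | 4.5 | 3.0 | 3.3 |
| 70% or 30% | 12.5 | 9.4 | 6.2 | 6.9 |
| 50% | 13.6 | 10.3 | 6.8 | 7.5 |

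(Half-widths in percentage points.)

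- For sensitivity of 95%, a half-width of 5 points needs 72.99 events: 72.99 / 260 = 28.1% of patients. At a 20% rate it needs 72.99 / 0.20 = 365 patients.
- For specificity of 95%, it needs 72.99 patients without an event, so it holds for any complication rate up to 1 − 0.281 = 71.9%.

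**3. Is 95% a realistic value against complications?** Sensitivity and specificity both at 95% correspond to an odds ratio of (0.95/0.05)² = 361 between a score and major complications. No such association is claimed anywhere in the article.

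**4. The odds ratio.** With a fraction r flagged, risks p1 and p0 satisfy r·p1 + (1−r)·p0 = π. The standard error of log OR is √(1/a + 1/b + 1/c + 1/d), where a to d are the four expected cell counts. The detectable odds ratio at 80% power and two-sided 5% solves log OR = (1.96 + 0.84) × SE.
- 10% flagged: about 3.3-3.4 over π = 20-35%.
- 30-50% flagged: about 2.5 at π = 20%, falling to 2.1-2.2 at π = 35%.

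Example: π = 20%, r = 30% gives SE = 0.320, and exp(2.80 × 0.320) = 2.45.

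At these odds ratios the sensitivity is about 17-68%, so the lower rows of the table are the relevant ones for sensitivity. With 10% flagged, specificity is about 93-94%, where 5 points is met.

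As an interval: a true odds ratio of 2.0 with 30% complications has an expected 95% interval of about 1.16-3.44 with 50% flagged and 0.88-4.56 with 10% flagged.

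**The case against.** The best defence is that 260 is a usable number whatever its derivation. The odds ratios will be reported with 95% intervals, so their actual precision will be visible, and the selection rule ranks lower bounds without setting a power target. That is fair, and it is why enrolment and analysis can stay as they are. It does not make the stated basis fit the analysis.

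Several stronger readings are tempting, and the article does not support them:

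- *That 260 gives the stated precision for none of the reported quantities.* Specificity near 95% keeps a half-width of about 3.0-3.3 points, and sensitivity of 95% reaches 5 points once the complication rate is about 28%.
- *That intervals are two to three times wider than stated.* This applies to sensitivity, if its true value is about 30-70% and the complication rate is in the assumed range. At 95% the ratio is only 0.9-1.2 (4.5/5 to 5.9/5).
- *That 70% contradicts counting only the highest class as at risk.* An assumed prevalence of a condition need not equal a score's top-class fraction, and three tools in Table 1 have only two classes. Likewise, 95%/95% accuracy with 70% flagged would need a complication rate of (0.70 − 0.05)/0.90 = 72%, but the article never says that a score will flag 70%.
- *That accuracy for malnutrition will never be estimated.* Validation of the ESPEN criteria is planned separately, in a way not described. One can say only that the analysis shown does not estimate it.
- *That 260 is an arithmetic error.* The stated inputs give 244, so 260 is on the safe side. A full width of 0.05 would need 72.99 × 4 / 0.30, or about 974, so that reading cannot be what was meant.

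**Conclusion.** The point holds as a mismatch between the planning target and the analysis. The sample size treats malnutrition as the condition to be detected; the analysis shown treats major complications as the condition; and the primary selection criterion does not enter the calculation. The 5-point precision is therefore not assured for sensitivity, nor for specificity well below 95%.

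The size depends on two assumptions that the article does not supply: a major complication rate of 20-35% and the true accuracy values. Within that range the sensitivity half-width runs from 4.5 points in the most favourable case to 13.6 points in the least, and the specificity half-width from 3.0 to 7.5 points. The defect lies in the stated justification. It does not show that 260 is too few.

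**What to change.** Keep 260 and replace the justification based on malnutrition prevalence. The new paragraph should state:

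1. an assumed major complication rate with its source and a range, and the expected number of events (52-91 if 20-35% is adopted);
2. the half-widths for sensitivity and specificity against major complications at realistic values, not only at 95%;
3. for the selection criterion, either the odds ratio detectable with 260 patients or its expected 95% interval, by fraction flagged (about 2.1-2.5 with 30-50% flagged and 3.3-3.4 with 10% flagged, at 80% power and two-sided 5%).

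The cost is one rewritten paragraph. Recruitment, data collection and the planned analyses do not change. The downside is that the stated precision will look less favourable than it does now.

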### Planned Study Conduct and Trial Visits

All patients visiting the Department of General, Visceral and Transplantation Surgery at the University Hospital of Heidelberg and scheduled to receive elective operations will be screened. Eligible patients will be consecutively informed about the study purpose and conduct. After giving a written informed consent, patients will be questioned and examined (Visit 1) according to the investigated nutritional assessment scores (Table 2). Further, other known risk factors for postoperative complications will be noted [32,33]. If the operation is delayed for any reason, patients will be re-evaluated as long as preoperative data from questionnaires are not older than 36 hours at the time of actual operation.

**Table 2 table2:** Flowchart of the NURIMAS trial-course of examinations.

Visit	1	2	3	4
	Preoperative	POD 3-7	POD 10-14	Discharge or POD 30
Eligibility	X			
Informed consent	X			
Baseline data	X			
Nutritional scores	X			
Laboratory analyses	X	x	x	x
Assessment of surgical procedure		x		
Assessment of complications		x	x	x
Serious adverse events		x	x	x
Secondary end points		x	x	x

After the operation, the clinical course will be followed prospectively. Therefore, 3 planned visits will be performed. The first visit will be performed on postoperative days (PODs) 3-7, the second visit on PODs 10-14, and the last visit on the day of discharge or not later than POD 30. During these visits, complications according to Textbox 2 [34-41] will be assessed. Every postoperative complication will be rated according to the validated classification by Clavien-Dindo [42]. Further, on postoperative visits, the status of secondary end points will be evaluated.

Assessed postoperative complications.• Postoperative pancreatic fistula [34]• Bile leak [35]• Postpancreatectomy hemorrhage [36]• Delayed gastric emptying [37]• Surgical site infection [38]• Other infections and sepsis [39]• Chylous ascites (triglycerides in drainage) [40]• Serious adverse event [41]

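### Major complications are assessed only until discharge (at latest POD 30), so the primary end point has a variable window, later events count as none, and the odds ratios may be distorted

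*Protocol article*

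**What the plan says.** All quotations are from the protocol article.

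- **End of observation.** Planned Study Conduct and Trial Visits states "Therefore, 3 planned visits will be performed": POD 3-7, POD 10-14, and "the last visit on the day of discharge or not later than POD 30". Table 2 heads the final visit "Discharge or POD 30" and has no column after it.
- **How events are found.** The same section says "During these visits, complications according to Textbox 2 [34-41] will be assessed". No telephone call, outpatient visit or readmission check after discharge is described.
- **End point.** Outcome Measures states "The primary end point is postoperative morbidity and mortality". It gives no time window and does not restrict the end point to the hospital stay.
- **Analysis.** Under Statistical Analysis, "patients will be dichotomized whether they had at least one major complication (Clavien-Dindo III-V) or not", and "Association between every nutritional assessment score and major complication will be expressed as odds ratio with 95% confidence interval". A chi-square test and a logistic regression follow. Nothing in that section allows for differing observation time.
- **Use of the result.** Outcome Measures picks the best score as the one whose OR has the highest lower 95% confidence limit. Length of stay is listed there as a secondary end point.

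**The concern.** A yes/no outcome compared by OR presumes that every patient had the same chance of being seen to have the event. Here that chance ends when the patient leaves. Someone discharged on POD 8 is observed for 8 days, and someone still in hospital is observed for up to 30. A reintervention, readmission or death on POD 20 in the first patient enters the contingency table as no major complication.

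Two consequences follow. First, events are missed, so the recorded rate is lower than the 30-day rate and sensitivity, positive predictive value and OR refer to a different quantity from the one the end point's name suggests. Second, if patients classed as at risk stay longer or shorter than the others for reasons unrelated to a complication already recorded, their events are captured more or less completely and the OR moves accordingly. Events that were never collected cannot be recovered at the analysis stage. The imputation mentioned under Minimizing Attrition Bias is aimed at incomplete outcome data, and under this schedule a discharged patient's record looks complete.

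**Working it through.** The article gives no length of stay, complication rate or onset timing, so there is no figure of its own to reproduce on this point. The sample size of 260 does not depend on the observation window. What follows is an illustration with assumed inputs.

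**Formula.** Let p be the true 30-day risk of a major complication in a group and c the share of those events that arise before discharge. The recorded risk is p × c, and

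recorded OR = [p1c1 / (1 − p1c1)] ÷ [p0c0 / (1 − p0c0)],

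with 1 = at risk and 0 = not at risk. A fixed 30-day window for everyone sets c0 = c1 = 1 and returns the true 30-day OR.

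**Assumed inputs.**
- True risk is 25% in both groups for the null case. For a true OR of 2.0 it is 25% versus 40%: odds 0.3333 × 2 = 0.6667, and 0.6667/1.6667 = 0.40.
- Onset is exponential with parameter 6, 9 or 12 days, truncated at day 30. The actual mean onset after truncation is 5.8, 7.9 and 9.3 days.
- Discharge day is log-normal with SD 0.35 on the log scale, drawn independently of complications.
- An event is recorded only if it precedes both discharge and day 30.

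**Capture c, by onset and median stay.**

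| Mean onset (days) | Stay 10 | Stay 12 | Stay 14 |
|---|---|---|---|
| 5.8 | 0.804 | 0.855 | 0.892 |
| 7.9 | 0.693 | 0.756 | 0.807 |
| 9.3 | 0.619 | 0.688 | 0.745 |

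Multiplied by 25%, these give recorded risks of about 15% to 22%.

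**No true effect, unequal stay (at risk longer).**
- 14 versus 10 days, early onset: 0.25 × 0.892 = 0.223 and 0.25 × 0.804 = 0.201; odds 0.287 and 0.252; OR 1.14.
- 14 versus 10 days, late onset: 0.1864 and 0.1548; odds 0.2291 and 0.1832; OR 1.25.
- 12 versus 10 days: OR 1.08 to 1.13 by the same steps.
- If the at-risk patients are the ones who leave earlier, the values invert: 1/1.08 = 0.93 to 1/1.25 = 0.80.

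**True OR 2.0, equal median stay of 10 days.**
- Early onset: 0.40 × 0.804 = 0.322 versus 0.201; OR about 1.88.
- Late onset: 0.40 × 0.619 = 0.248 versus 0.155; OR about 1.80.

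**Equal stay, no true effect.** c0 = c1 and p0 = p1, so the OR stays at 1.00.

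**Check by a simpler model.** Discharge on a fixed day, 30-day risk 20% to 30%, exponential onset with parameter 5 to 10 days (truncated at day 30), day 14 versus day 10: a true OR of 1.0 is recorded as 1.11 to 1.25, in line with the range above.

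**The case against.** The strongest reply is that bias is possible but not shown. Upward bias needs at-risk patients to stay longer for reasons other than a major complication already recorded, and the documents say nothing about that. Much of the real link between stay and complications runs the other way: complications prolong stay, which is not an ascertainment problem. The illustration draws discharge independently of complications, so it places 11% to 38% of 30-day events after discharge (1 − 0.892 to 1 − 0.619), and no figure in the documents supports that share. If capture were 90% versus 93%, or 95% versus 97%, a true OR of 1.0 at 25% risk would be recorded as only 1.04 or 1.03. All of this stands, and it limits what can be claimed about size and direction.

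The shift is also modest against precision. With 260 patients, 30% to 70% at risk and 18% to 25% events (assumed), the standard error of the log OR is about 0.29 to 0.35. A spurious 1.08 to 1.25 is 0.08 to 0.22 on that scale, less than one standard error. All 12 scores share the same outcome data, so their ranking changes only as far as they differ in their relation to stay. This stands too.

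Three stronger readings are tempting, and the documents do not support them:
- **That the schedule creates an association between malnutrition and complications.** The direction is open. Listing length of stay as a secondary end point does not state that it is expected to be longer in malnourished patients.
- **That length of stay and place of discharge are cut off at POD 30.** No section says so. The cost and DRG end points suggest that hospital administrative data are used, and the source of discharge dates is a detail an article may leave to the full protocol.
- **That early-discharged patients lose events by missing the POD 10-14 visit.** The discharge visit also assesses complications, so nothing that happened in hospital is lost.

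Finally, in-hospital morbidity is a legitimate end point. But the article does not call it that, and its aim is to predict postoperative complications in general. The schedule is stated both in the text and in Table 2, so this is not a detail left out for brevity.

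**Conclusion.** The point holds in a limited form. As published, the window for the primary end point is the hospital stay, capped at POD 30, and major events after discharge but before POD 30 are counted as no complication. Three things follow: events are undercounted to the extent that they occur after discharge; with equal capture a real association shrinks towards 1 while a null one stays at 1; with unequal capture the OR may move either way.

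The illustrated shifts (about 8% to 25% on a null OR, about 6% to 10% off an OR of 2.0) rest entirely on assumed risk, onset and stay, and on discharge being independent of complications. They show that the effect need not be negligible. They do not estimate it for this trial. The individual ORs, sensitivities and predictive values are more exposed than the ranking of the scores. The change is worth making because it is cheap and the lost information cannot be restored later.

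**What to change.** Define the primary end point as at least one Clavien-Dindo III-V complication by POD 30 for every patient. Keep the discharge visit. For patients discharged earlier, obtain POD-30 status (readmission, reintervention, death) from hospital records plus one short telephone call, and add this to Table 2. The cost is a minor amendment and one record check and brief call per discharged patient, for 260 patients at a single centre.

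If that is not possible, define the end point explicitly as in-hospital complications up to POD 30 in Outcome Measures, and limit the conclusion about the most predictive score to that end point. This costs only wording, but it leaves the dependence on length of stay in place, which should then be stated as a limitation.
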